### 2.2. Patient Monitoring

When epithelialisation is complete, treatment and visits from the home nurses will be stopped. Follow-up will be carried out by the referent nurses, who will visit the patient monthly or see him/her in hospital to check the wound, take a picture of the wound and collect information in case of a new hospitalization, relapse, or other important events until Week 24. The duration of the participation in the study: 16 weeks/patient + 8 weeks follow-up with a focus on wound healing at 16 weeks.

### 2.3. Photography

The ulcer is photographed before debridement/cleaning, after debridement/cleaning if that is deemed necessary, and after placement of Kerecis Omega3 Wound (if applicable) with a centimetre scale and patient identifier placed in the photo. An acetate tracing (outline of the ulcer on transparent plastic) is made and photographed where a centimetre scale and a patient identifier is visible in the photo. Photos are uploaded via the Smart-Trial^®^ portal as a part of filling out the case report form). The largest diameter, and the diameter perpendicular, is measured at all visits.

Three status checkpoints are imbedded in the study:i.Has the wound changed its grade, i.e., have the granulations covered bone and tendon? Answered by clinician since the answer is dependent on probing to bone.ii.Is the wound ready for standard of care only, to commence healing? Answered by clinician and blinded panel of clinicians.iii.Would a split thickness skin graft be a logical next intervention? Answered by blinded panel only.

### 2.4. Statistical Methods

The null and alternative hypotheses are:▪H0: no difference in the percentage of patients cured with complete epithelialization at 16 weeks between Kerecis Omega3 Wound and the SOC.▪H1: a percentage difference in the number of patients cured with complete epithelialization at 16 weeks between Kerecis Omega3 Wound and SOC.▪It is expected that 30% of patients will have healed with complete epithelialization at 16 weeks in the SOC group [see point below].▪A 20% improvement with Kerecis Omega3 Wound (i.e., 50% of patients healed) would be considered clinically significant.▪A Fisher’s exact conditional test with a two-sided significance level of 0.05 will have 80% power to detect the difference between a Group 1 proportion of 0.3 and a Group 2 proportion of 0.5 for a size d sample in each group of 90.▪Assuming an attrition rate of 10%, 180 patients (=190/0.9) will need to be randomized in this trial.

Statistical analysis will be performed using SAS^®^ software, version 9.4.0 or higher. Analysis of the primary endpoint (i.e., the percentage of patients healed with complete epithelialization at 16 weeks) will be conducted using Fisher’s exact test. The 95% confidence intervals of the proportions in each group will be displayed.

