### 2.1. Conduct of the Study

This study uses the Smart-Trial^®^ electronic platform for gathering data, obtaining CRFs, and monitoring of the study. The study design is demonstrated in Figure 1. Randomisation will take place after inclusion via the electronic case report form. The randomisation list is in blocks of two; the stratification will be performed according to two criteria: amputation and non-amputation wounds and ABI (≤0.9 and >0.9). Patients will then be assigned either to the conventional treatment group (control group), or to the interventional group, where they will be treated with Kerecis Omega3 Wound. The hospital investigator will assess the wound status of patients in both groups during hospital visits at the following times:Week 7: patients come to the hospital for the investigator to assess wound progress.Week 16: end of study visit after the last application of Kerecis Omega3 Wound. An HbA1c measurement will be collected.Week 20: patients come to the hospital for the investigator to assess the progress of the wound.Week 24: at the end of the two-month follow-up period an HbA1c measurement will be collected.

The referral nurse (RN) and the home nurses (HNs) for the study in each centre will receive theoretical and practical training from a Kerecis professional specialized in wound care.

In the study, the difference between the standard of care group and the interventional group is that Kerecis Omega3 Wound is applied between the dressing, that would otherwise contact the ulcer, and the ulcer bed. The dressing on top of Kerecis Omega3 Wound then becomes the covering dressing. In the control group, the care is the same whilst there is no Kerecis Omega3 Wound under the covering dressing. Most often, the covering dressing would be a foam dressing. The different approaches for using offloading in different clinics will adhere to the International Working Group on the Diabetic Foot’s Guidelines [10].

Kerecis Omega3 Wound is applied once per week for the first six weeks, and every other week for the remaining 8 weeks of active intervention, with up to 10 applications in total. If complete epithelialization is achieved, the application will be stopped. Both groups will receive standard of care for the last two weeks (Weeks 15 and 16). For both groups each week, when the home nurse takes a picture of the wound, he/she will ask the patients to fill in a visual analogue scale (VAS) for perception of pain.

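### With 90 patients per group the planned two-sided Fisher's exact test has about 75% power for 30% versus 50%, not the stated 80%

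*Protocol article*

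**What the plan says.** The protocol article, section 2.4 (Statistical Methods), sets out the sample-size calculation in full.

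- Control rate: "It is expected that 30% of patients will have healed with complete epithelialization at 16 weeks in the SOC group".
- Target effect: "A 20% improvement with Kerecis Omega3 Wound (i.e., 50% of patients healed) would be considered clinically significant".
- Test, level and power: "A Fisher’s exact conditional test with a two-sided significance level of 0.05 will have 80% power to detect the difference", followed by "between a Group 1 proportion of 0.3 and a Group 2 proportion of 0.5 for a size d sample in each group of 90".
- Primary analysis: it "will be conducted using Fisher’s exact test".
- Number to randomise: "Assuming an attrition rate of 10%, 180 patients (=190/0.9) will need to be randomized in this trial".

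Equal allocation follows from the single group size and from section 2.1: "The randomisation list is in blocks of two".

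**The concern.** Fisher's exact test is conservative. With group sizes near 100 its true type I error lies well below the nominal 5%, and it needs noticeably more patients than an uncorrected chi-square test for the same power. For 30% versus 50%, 90 per group is about what the uncorrected formulas give, so 80% looked too high for Fisher's test.

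The power statement is the only justification given for the trial's size, and it is the yardstick against which a non-significant result will be read. If power is overstated, a null result looks like stronger evidence against a 20-point benefit than it is.

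**Working it through.** **Inputs, all from section 2.4:** two-sided Fisher's exact test, α = 0.05, p₁ = 0.30, p₂ = 0.50, n = 90 per group, stated power 80%.

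**Step 1. Where 90 could come from.** Use z₀.₉₇₅ = 1.960 and z₀.₈₀ = 0.8416.

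- Unpooled normal formula: n = (p₁q₁ + p₂q₂)(1.960 + 0.8416)² / (p₂ − p₁)² = (0.21 + 0.25) × 7.849 / 0.04 = 90.3.
- Pooled (chi-square) formula, with mean rate 0.4: n = [1.960 × √(2 × 0.4 × 0.6) + 0.8416 × √0.46]² / 0.04 = (1.3579 + 0.5708)² / 0.04 = 93.0.
- Arcsine formula: 92.7.

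So 90 per group is reproduced, approximately, only by uncorrected large-sample formulas. None of them describes Fisher's test.

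**Step 2. Power of the named test.** Let X ~ Binomial(90, 0.3) and Y ~ Binomial(90, 0.5), independent. For each table (x, y), the two-sided Fisher p-value is the sum of the hypergeometric probabilities, given x + y, that do not exceed that of the observed table. Then

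power = Σ P(X = x) · P(Y = y), summed over all tables with p ≤ 0.05.

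| n per group | Exact power, two-sided Fisher |
|---|---|
| 81 | 68.6% |
| 90 | 74.9% (0.7485) |
| 95 | 76.0% |
| 101 | 79.9% |
| 102 | 80.6% |

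Doubling the smaller tail instead of summing the less likely tables gives the same values, so the choice of two-sided definition does not explain the gap.

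**Step 3. Cross-checks.**

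- The continuity-corrected formula, which approximates Fisher's test, needs 103 per group. At 90 it gives a power of 73.9%.
- The uncorrected chi-square test at 90 per group has an exact power of 79.3% (78.7% by formula). This is close to the stated 80%.
- Fisher's actual type I error at 90 per group is 3.1% to 3.7% for common healing rates between 0.3 and 0.5. That is where the power is lost.
- With 90 per group and 30% in the control arm, Fisher's test reaches 80% power only if the true rate on treatment is about 51.3%.

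**Step 4. Other readings of the text.**

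- One-sided 0.05 Fisher's test at 90 per group: 84.2%. This is not 80%, and the text says two-sided.
- Printed 190 read as the evaluable total (95 per group): 76.0%.
- 180 randomised less 10% (180 × 0.9 = 162, or 81 per group): 68.6%.

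No reading gives 80% for the test named.

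**The case against.** Nobody can reasonably contest the arithmetic. The case on the other side concerns its weight and its setting.

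*Small and harmless to validity.* The gap is 5 points of power. It does not bias the estimated difference, and the conservatism of Fisher's test protects the type I error. The abstract says that inclusion ended in July 2022, so a correction changes no enrolment and no data. All of this is true. It limits the consequence to how the design is justified and how a null result is read, but it does not make the sentence right.

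*The paragraph is garbled anyway.* The group-size phrase is mangled, and 190/0.9 is 211, not 180, so one may doubt which evaluable number was intended. The doubt is fair, but it does not help: neither 90 nor 95 per group reaches 80%. Since 180 is exactly 2 × 90, the number to be randomised contains no allowance for the 10% attrition. That is a separate error, and it makes 75% the favourable figure.

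*The larger study.* Section 2 describes the French trial as part of an overarching study planned at 330 patients. With 165 per group, Fisher's power would be 95.2%. If the confirmatory inference rested on that total, the one-in-four risk would not apply to it. But the power sentence is about 90 per group, and the Conclusions repeat 180 as the number to be enrolled.

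**Conclusion.** The concern holds. For the test, level, rates and group size in section 2.4, power is 74.9%, not 80%. The false-negative risk at the design effect is about 25% instead of 20%. An 80% target with this test needs 102 per group, or 204 evaluable patients: 24 more than 180. With 10% attrition that would be 204/0.9, about 227 randomised.

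The result rests on the document's own inputs, on equal allocation, and on all 90 patients per group being evaluable. If 10% of the 180 randomised are lost, power falls to about 69%.

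**What to change.** Correct the sample-size sentence so that the figure belongs to the test named, for example: *With 90 evaluable patients per group, a two-sided Fisher's exact test at the 0.05 level has 75% power to detect 30% versus 50% healed.* In the same edit, reconcile 180, 190 and the 10% attrition. If 180 is the number randomised and 10% are expected to be lost, report the power at 81 per group (about 69%) as well.

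The cost is a change of wording and a less favourable power figure. No extra patients are needed, and the primary test stays as it is.

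A stratified Cochran-Mantel-Haenszel test on the two randomisation factors is a possible alternative primary test, but it is not needed for this correction. Assuming four near-equal strata with nil to moderate effects, simulation puts its power at 90 per group at 79–82% without continuity correction and 74–77% with it. The documents do not give the strata effects, so these figures are only indicative. Such a change is acceptable only if it is fixed before anyone sees comparative outcome data, and the power statement would then have to be recomputed for that test. Otherwise the restatement alone is the correction.

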## 4. Conclusions

The aim of the KereFish and larger Odin study is to demonstrate the superiority of Kerecis Omega3 Wound over SOC in the treatment of diabetic wounds. 180 patients should be enrolled at the end of the inclusion period which is end of July 2022 and the first results are planned to be published in March 2023.

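### The 180 patients to be randomised contain no allowance for 10% attrition: 190/0.9 is 211, 180 is simply 2 × 90, and after the stated loss Fisher power is about 69%

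*Protocol article*

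**What the plan says.** All the sample-size inputs are in section 2.4 (Statistical Methods) of the protocol article. The design test is Fisher's: "exact conditional test with a two-sided significance level of 0.05 will have 80% power". The rates are a "Group 1 proportion of 0.3 and a Group 2 proportion of 0.5", and the required number is given as "for a size d sample in each group of 90". The next bullet adds the attrition step: "Assuming an attrition rate of 10%, 180 patients (=190/0.9) will need to be randomized in this trial". The same section names Fisher's exact test for the primary analysis, so design and analysis use the same test.

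Section 4 (Conclusions) repeats the number as the recruitment target: "180 patients should be enrolled at the end of the inclusion period".

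**The concern.** The attrition sentence makes two claims, and neither agrees with the rest of the section. It says that 180 equals 190/0.9, and it says that 180 already covers a 10% loss. The bullet before it needs 2 × 90 = 180 patients before any loss, so the total to be randomised equals the total to be evaluated. The 190 appears nowhere else and is not twice 90.

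This is the sample-size justification for the primary endpoint. A reader will take it that the trial keeps 80% power after losing one patient in ten. If the result is not significant, that reader will judge the chance of having missed the target effect to be 20%, when on the plan's own figures it is nearer one in three.

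**Working it through.** **Inputs (section 2.4).** Two-sided Fisher's exact test, alpha 0.05; 30% healed on standard of care versus 50% on the fish skin graft; 90 per group; 10% attrition; 180 randomised. Equal allocation follows from the equal group size.

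**Step 1: the printed equation.** The usual inflation is N randomised = N evaluable / (1 − attrition).

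| Starting figure | Divided by 0.9 | Multiplied by 1.1 |
|---|---|---|
| 190 (as printed) | 211.1 (212 rounded up) | 209 |
| 2 × 90 = 180 | 200 | 198 |
| 162 | 180 | 178.2 |

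Neither form gives 180 from 190 or from 2 × 90. Only 162/0.9 gives 180, and 162 is not in the document. Exchanging the two figures does not help, because 180/0.9 is 200 and not 190.

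**Step 2: what 180 randomised delivers.** 180 × (1 − 0.10) = 162, or 81 per group.

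**Step 3: power.** Exact power of the two-sided Fisher test is the sum of Binomial(n, p1) × Binomial(n, p2) probabilities over all tables with Fisher p ≤ 0.05.

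| Per group | Rates | Situation | Fisher power |
|---|---|---|---|
| 90 | 30% vs 50% | plan's figure, no loss (stated as 80%) | 74.9% |
| 81 | 30% vs 50% | 10% lost and excluded | 68.6% |
| 90 | 27% vs 45% | 10% lost, kept as not healed | 66.8% |
| 95 | 30% vs 50% | 190 evaluable | 76.0% |
| 102 | 30% vs 50% | smallest tabulated n above 80% | 80.6% |

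The third row uses 0.9 × 30% = 27% and 0.9 × 50% = 45%. At 101 per group, power is 79.9%.

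The plan's 80% at 90 per group is therefore not reproduced with the test it names. An uncorrected chi-square test comes close (78.7% by the normal approximation). At 81 per group that test gives 73.9% by enumeration and 74.3% by the approximation, so the post-attrition power is below 80% under either test.

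**Step 4: splitting the shortfall.** 80% − 74.9% = 5.1 points come from the power at 90 per group, which is a separate error. A further 74.9% − 68.6% = 6.3 points come from the missing attrition allowance.

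**Step 5: detectable effect.** With 81 per group and 30% on standard of care, a healing rate of 52.8% in the graft arm gives 79.9% Fisher power. About 80% power therefore needs a difference of nearly 23 points instead of 20.

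**The case against.** The arithmetic is not open to dispute, but four points can be made about its weight.

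- **Attribution.** Setting 69% against 80% suggests that attrition explains the whole gap, when about 5 of the roughly 11 points are lost at 90 per group before anyone drops out. This stands, and the size given here is 75% to 69%.
- **Source of the slip.** The bullets are visibly garbled and the article condenses a fuller protocol. A mistranscribed figure is possible. If 190 meant 95 per group, an uncorrected chi-square test would give about 81% power, but 211 would then have to be randomised. Every such repair conflicts with another printed number, and the Conclusions confirm 180 as the target. The uncertainty about the source stands, so the full protocol should be consulted. It does not rescue the statement.
- **Conditionality.** The 69% assumes that lost patients are excluded and that losses are equal in the two arms. The article gives no missing-data rule and may leave that to the analysis plan. Counting lost patients as not healed gives 67%, so the conclusion does not turn on this choice.
- **Consequence.** The abstract says that inclusion ended in July 2022, and 180 belongs to the French part of a larger study planned at 330. The error does not touch the endpoint, the type I error or the estimate. That limits the remedy to wording. However, section 2.4 ties 180 to this trial's own hypothesis test, and the 330 explains neither 180 nor 190.

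**Conclusion.** The concern holds. The printed equation is false, and 180 randomised contains no attrition allowance. At the plan's own 10% loss, two-sided Fisher power for 30% versus 50% is 68.6% with lost patients excluded equally from both arms, or 66.8% with them counted as not healed. The chance of missing the effect that the plan calls clinically significant is thus 31% to 33%, against the 20% stated. The missing allowance accounts for the fall from about 75% to about 69%. The rest of the gap is the overstated power at 90 per group.

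**What to change.** Check the figures 90, 180 and 190 against the full protocol and reconcile them. Unless that check changes the number randomised, remove the bracketed equation and the claim that 180 covers attrition, and replace them with wording such as:

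> 180 patients will be randomised. With 10% attrition, about 162 (81 per group) are expected to be evaluable. If lost patients are excluded, this gives about 69% power with the two-sided Fisher's exact test for healing rates of 30% and 50%; if they are counted as not healed, power is about 67%.

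Keep whichever power figure matches the analysis set and missing-data rule actually used. Add for transparency that 180 evaluable patients would have required 200 randomised, and that 200 would still give only about 75% Fisher power. To reach 80% with that test takes about 102 evaluable per group, that is 204 in total, or 204/0.9 ≈ 227 randomised.

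The cost is a change of wording and a less favourable stated power. Enrolment, endpoint and test are unaffected.

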## 2. Materials and Methods

This study, KereFish, is the French part of a multinational clinical trial taking place in France, Germany, Italy, and Sweden. The overarching study, Odin, is a multi-national, multicentric, randomised, controlled, open-label, interventional study comparing the use of Kerecis Omega3 Wound with conventional therapy (SOC, Standard of Care) in the treatment of complex, hard-to-heal, diabetic foot wounds with a planned total of 330 patients.

Primary objective: To demonstrate the superiority of Kerecis Omega3 Wound over SOC in the treatment of severe diabetic wounds with or without a moderate arterial component.

Secondary objectives: The secondary objectives are to: (i) Evaluate the safety of Kerecis Omega3 Wound. (ii) Assess secondary clinical efficacy endpoints. (iii) Assess patient and caregiver satisfaction. (iv) Assess the impact on patient quality of life. (v) Assess the economic impact of Kerecis Omega3 Wound treatment on patient care costs and to determine the effectiveness of this treatment.

Primary endpoint: Percentage of healed wounds with complete epithelialisation at 16 weeks.

Secondary endpoints: Change in ulcer grade according to the University of Texas diabetic wound classification at each weekly visit. Change in quality of life. Change in pain. Healing trajectory. Cost effectiveness. Number of participants with fully healed ulcers at 20 weeks. Number of participants with fully healed ulcers at 24 weeks. Percentage of ulcers healed 50% or more at 12 weeks.

Inclusion criteria: People living with diabetes of any age with diabetic foot ulcer Grade 2 or 3 according to the University of Texas (UT) diabetic foot classification system [13]; Grade 2: wound penetrating to the tendon or capsule. UT Grade 3: wound penetrating to bone or joint, OR patients admitted/ambulatory for diabetic foot wounds or amputations, which have not closed or are dehiscent. Patients who can tolerate aggressive surgical debridement. Patients without severe ischaemia; ankle brachial index (ABI) > 0.6 or big toe pressure > 50 mmHg if ABI is not possible. Wound age ≥ 30 days (does not apply to amputation wounds; patients can be included when the wound is less than 30 days old) or if the amputation level is below the ankle. Patients willing and able to give informed consent to participate in the clinical trial. Male or female over 18 years of age. Patients living at a geographical distance compatible with the home nurse.

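### The primary analysis is an unstratified Fisher's exact test although randomisation is stratified by amputation status and ABI: valid, but conservative and short of power

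*Protocol article*

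**What the plan says.** Section 2.1 of the protocol article describes the randomisation: "The randomisation list is in blocks of two", and "the stratification will be performed according to two criteria: amputation and non-amputation wounds and ABI (≤0.9 and >0.9"). That makes 2 × 2 = 4 strata, with the arms kept almost equal inside each.

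Section 2.4 names the primary test: "Analysis of the primary endpoint (i.e., the percentage of patients healed with complete epithelialization at 16 weeks) will be conducted using Fisher’s exact test". Neither stratification factor enters it. The sample size rests on the same unstratified test: "A Fisher’s exact conditional test with a two-sided significance level of 0.05 will have 80% power" at 90 per group, for 30% healed on standard of care against 50% on the graft. The interval output is described in one sentence: "The 95% confidence intervals of the proportions in each group will be displayed".

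The eligibility criteria in section 2 also admit patients by "big toe pressure > 50 mmHg if ABI is not possible". Section 2.1 lists no ABI category for them.

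**The concern.** The design goes to the trouble of balancing two factors, and the named primary test makes no use of that. Two separate inefficiencies result.

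- **Discreteness.** A two-sided Fisher test at nominal 0.05 rejects less often than 5% under the null at these sample sizes, so it also rejects less often under the alternative.
- **Unused balance.** Where a factor predicts healing, balancing it lowers the true variance of the between-arm difference. An unstratified test still works with the larger variance and becomes more conservative again.

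What is at stake is power, not the false-positive rate. Recruitment closed in July 2022, so the choice of analysis is one of the few ways left to recover power without more patients. A lesser point is that the clinical target is a 20-point difference, whereas the only interval the article mentions is one for each arm.

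**Working it through.** **Inputs from section 2.4:** healing 0.30 and 0.50, two-sided 0.05, 90 per group, 10% attrition, 180 randomised. Since 180 = 2 × 90, 10% attrition would leave 0.9 × 90 = 81 per arm, so both sizes are shown. **From section 2.1:** four strata and blocks of two. **From section 2:** parent trial of 330, or 165 per arm. **Assumed, because the article gives no figures:** four equal strata, and an odds ratio for healing of 1 to 3.5 for each factor, with the overall rates held at 0.30 and 0.50.

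**1. The plan's own figure.** Exact power is Σₓ Σᵧ b(x; n, 0.3) · b(y; n, 0.5) · 1[Fisher p(x, y) ≤ 0.05], summed over all 2 × 2 tables.

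- n = 90: 74.9%, against the stated 80%.
- n = 81: 68.6%.
- n = 102: 80.6%.

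The stated 90 agrees with the unpooled normal approximation: (1.960 + 0.842)² × (0.21 + 0.25) / 0.04 = 90.3. That is not the test the text names.

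**2. Why ignoring the strata costs power.** Take an odds ratio of 2.7 per factor. The control rates in the four strata are then about 0.51, 0.28, 0.28 and 0.13 (mean 0.30). The mean within-stratum variance is (0.250 + 0.202 + 0.202 + 0.113) / 4 = 0.192. The unstratified test uses 0.30 × 0.70 = 0.210. The within-stratum variance is about 9% smaller, and only a stratified test uses it.

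**3. Power of the alternatives.** CMH statistic without continuity correction: [Σₖ(xₖ − Eₖ)]² / ΣₖVₖ, where Eₖ and Vₖ are the hypergeometric mean and variance in stratum k. There were 200,000 simulations per row, so the simulation error is about 0.1 point. The Pearson chi-square column separates the two causes. Fisher to chi-square is discreteness; chi-square to CMH is the omitted strata.

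| Per arm | OR per factor | Fisher % | Chi-square % | CMH % | Discreteness | Strata | Total |
|---|---|---|---|---|---|---|---|
| 81 | 1.0 | 68.5 | 73.8 | 73.7 | 5.3 | −0.1 | 5.2 |
| 81 | 2.0 | 68.9 | 74.3 | 76.7 | 5.4 | 2.3 | 7.7 |
| 81 | 2.7 | 69.3 | 74.7 | 78.9 | 5.4 | 4.2 | 9.7 |
| 81 | 3.5 | 69.8 | 75.5 | 80.9 | 5.7 | 5.4 | 11.1 |
| 90 | 1.0 | 74.9 | 79.3 | 79.0 | 4.4 | −0.3 | 4.1 |
| 90 | 2.0 | 75.4 | 79.9 | 81.2 | 4.5 | 1.3 | 5.8 |
| 90 | 2.7 | 75.8 | 80.4 | 82.7 | 4.6 | 2.3 | 6.9 |
| 90 | 3.5 | 76.4 | 81.0 | 84.7 | 4.5 | 3.7 | 8.3 |
| 165 | 1.0 | 95.2 | 96.2 | 96.2 | 1.0 | 0.0 | 1.0 |
| 165 | 3.5 | 96.4 | 97.2 | 98.1 | 0.8 | 0.9 | 1.7 |

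Differences are taken before rounding. Unequal strata (40/30/20/10%) change little: at 2.7 per factor the total gap is 9.0 points at 81 and 6.2 at 90.

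**4. Type I error at 81 and 90 per arm.** Fisher's actual level is 0.031 to 0.037 when the factors do not matter, about 0.026 at an odds ratio of 2.7 per factor, and about 0.02 at 4.5. CMH stays near 0.050 throughout.

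**5. What an interval for the difference adds.** Take 41/90 against 27/90, a difference of 15.6 points. Fisher p = 0.045. The arm intervals, 35 to 56% and 21 to 41%, overlap. The Newcombe interval for the difference is 1.4 to 28.9 points.

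**The case against.** **The plan is consistent with itself.** It sizes the trial on Fisher's test and analyses with Fisher's test, so the conservatism was meant to be paid for in the sample size, and the test protects the type I error. All of this stands, except that the payment falls short: 90 per group gives 74.9%. That shortfall is a sample-size error in its own right and does not itself show that the analysis should be stratified.

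**A reader might infer that ignoring the strata causes the whole loss of about 4 to 11 points.** The table does not support that. In every row at 81 or 90 per arm, discreteness costs more than the omitted strata, and it would do so without any stratification.

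**A reader might also take it as given that the factors were chosen because they predict healing.** Section 2.1 gives no reason. The introduction calls arterial disease the most severe prognosis, but for amputation and mortality. No healing rates by stratum are given, so the upper end of the range is an assumption.

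**The article is condensed.** An interval for the difference may well be in the full analysis plan. The article does not exclude it, and the two proportions already give the point estimate. The success decision rests on Fisher's p-value, not on whether arm intervals overlap. This part is secondary. The primary test is different: the article names it outright rather than leaving it open.

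**Timing.** Section 2 calls the overarching trial open-label, and recruitment had ended before the article appeared. Moving to a less conservative primary test at that stage can look like a choice made after the fact. That is a real cost and governs how the change has to be made.

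**Conclusion.** The point holds as one of efficiency. The named primary test does not match the stratified randomisation and is conservative, with an actual level of about 0.02 to 0.04. Its results would be valid, and nothing here suggests a raised false-positive risk.

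For the 180-patient trial the loss against a stratified CMH test is about 4 to 8 points at 90 per arm and 5 to 11 at 81. Of this, 4 to 6 points are due to Fisher's discreteness and need no assumption about the strata. The other 0 to 5 or so come from ignoring them and depend on assumed odds ratios of 1 to 3.5 per factor. If the factors do not predict healing, stratifying gains nothing beyond dropping the exact test. If the primary analysis is that of the 330-patient parent trial, the total loss is only about 1 to 2 points. The change is worth making, but the trial does not stand or fall by it.

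**What to change.** Before unblinding or any comparative look at the data, and documented as an amendment:

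1. Make the primary test a CMH test without continuity correction, stratified by amputation status and ABI (≤0.9, >0.9) at the levels recorded at randomisation.
2. Patients without a measurable ABI keep the stratum in which they were randomised. A third ABI level would depart from the randomisation strata, so none should be added.
3. Report the stratified risk difference with its 95% confidence interval beside the two arm proportions.
4. Keep the unstratified Fisher test as a sensitivity analysis.
5. Restate the power for the test chosen.

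The cost is analysis wording, since the stratum is fixed for each patient at randomisation. The small downside is a documented change of primary test after recruitment closed in an open-label trial. The amendment should therefore give its date, state that no comparative data had been seen, and rest on the randomisation design.

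### The primary Fisher's test makes no use of baseline wound size, which the trial measures but does not stratify on; the cost is some precision, not bias

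*Protocol article*

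**What the plan says.** - **Primary test.** Section 2.4 says the analysis of the proportion healed at week 16 "will be conducted using Fisher’s exact test", with a 95% confidence interval for each group's proportion. No covariate or stratum enters the test.
- **Sample size.** Section 2.4 also says: "A Fisher’s exact conditional test with a two-sided significance level of 0.05 will have 80% power", for "a Group 1 proportion of 0.3 and a Group 2 proportion of 0.5", "for a size d sample in each group of 90".
- **Baseline size.** Section 2.3: "The largest diameter, and the diameter perpendicular, is measured at all visits". An acetate tracing is also made and photographed.
- **Stratification.** Section 2.1: "the stratification will be performed according to two criteria: amputation and non-amputation wounds and ABI". Wound size and depth are not among the factors.
- **Depth.** Section 2 (inclusion criteria) admits University of Texas (UT) grades 2 and 3: "Grade 2: wound penetrating to the tendon or capsule. UT Grade 3: wound penetrating to bone or joint". An alternative route, joined by OR, admits diabetic foot wounds or amputations that are unclosed or dehiscent, and it requires no UT grade.

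**The concern.** The endpoint is full closure by a fixed week. A larger wound has more surface to cover in the same time, so baseline size is a natural predictor of the outcome. The measurement is already collected. A test that ignores it treats predictable variation between patients as noise, and the estimate carries the full effect of any chance difference in size between the arms.

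What is at stake is power and the stability of the estimate. Both matter more here because the design has no slack: the stated Fisher's test does not reach its stated power at the stated group size (shown in the working).

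**Working it through.** **Inputs from section 2.4:** healing 0.30 and 0.50, two-sided 0.05, 90 per group, Fisher's test, 10% attrition, 180 randomised. **Assumed, because the article gives no figure:** baseline log size, standardised, has a log odds ratio for healing of -0.4, -0.7 or -1.0 per SD.

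**1. The plan's own figure.** Exact enumeration of Fisher's test at 90 per group gives 74.9% power, not 80%. At 101 per group it gives 79.9% and at 102 it gives 80.6%. The uncorrected chi-square approximation gives 78.7% at 90. The attrition line, "Assuming an attrition rate of 10%, 180 patients (=190/0.9) will need to be randomized in this trial", does not work either: 190/0.9 = 211. If 180 are randomised and 10% are lost, 180 × 0.9 = 162 remain, or 81 per group, and Fisher power is 68.6%. These are separate faults, given here only as context.

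**2. Power with adjustment, 90 per arm.** Simulation of 6,000 trials per row, with a logistic model calibrated to marginal rates of 0.30 and 0.50:

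| Log OR per SD | Fisher | Chi-square | Adjusted for size | Covariate gain (adjusted minus chi-square) | Change of test only (chi-square minus Fisher) |
|---|---|---|---|---|---|
| 0 | 74.2% | 78.9% | 78.6% | -0.3 | 4.7 |
| -0.4 | 75.6% | 79.8% | 80.9% | 1.1 | 4.2 |
| -0.7 | 74.8% | 79.8% | 83.4% | 3.6 | 5.0 |
| -1.0 | 75.0% | 79.2% | 85.9% | 6.7 | 4.2 |

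The row at 0 shows why the two gains must be kept apart. A useless covariate still appears to gain 78.6 - 74.2 = 4.4 points over Fisher, all of it from leaving a conservative test.

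A second simulation (4,000 trials per setting) adjusted for size and for UT grade, assuming a 50/50 grade split and the same odds ratio for each. At odds ratios of 1.5, 2, 2.5 and 3, adjusted power was 80.5%, 83.5%, 84.2% and 87.2%, against 79.7%, 79.9%, 78.4% and 78.4% for chi-square. The gain is about 1 to 9 points when both covariates carry information.

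**3. Type I error.** Fisher's test rejected in 3.5% to 3.6% of simulated null trials. The adjusted test rejected in 5.0% to 5.3% across slopes -0.4 to -1.0 in the first simulation and 5.1% to 5.2% in the second. With a useless covariate the first simulation gave 5.7% and the second 5.1%.

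**4. Chance imbalance.** The SD of the between-arm difference in standardised log size is √(2/90) = 0.149. The probability of a difference of at least 0.2 SD is 2 × [1 - Φ(0.2/0.149)] = 0.18.

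The shift in the healed-rate difference from a 0.2 SD imbalance is approximately 0.2 × |slope| × mean of p(1 - p), where p is the patient's healing probability given size:

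- Mean p(1 - p) in the control arm is 0.203, 0.192 and 0.177 for the three slopes, so the shift is 1.6, 2.7 and 3.5 points.
- Averaged over both arms it is 0.222, 0.208 and 0.192, so the shift is 1.8, 2.9 and 3.8 points.

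The standard error of the difference is √(0.30 × 0.70/90 + 0.50 × 0.50/90) = 0.0715, or 7.1 points. A shift of 1.6 to 4 points is therefore 1.6/7.15 = 0.22 to 4/7.15 = 0.56 standard errors.

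**The case against.** The strongest reply is that nothing here is wrong. Fisher's test is valid in a randomised trial. Randomisation balances size in expectation, and the test's sampling error already allows for chance imbalance in either direction. Stratifying on amputation may capture part of the variation in size and depth. All of this stands. A reader might infer that the primary result would be biased or its type I error inflated; the documents do not support that.

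Second, the article does not show that baseline size or depth determines closure. Its Discussion links healing to the reduction in size over 4 weeks, which is measured after randomisation and is at most indirect support. The prognostic strength is therefore an assumption, and at its weakest the gain is about 1 point. The absence of a size limit among the printed inclusion criteria adds little, because an article may omit exclusion criteria that the full protocol contains.

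Third, a reader might compare the adjusted model directly with Fisher's test and claim 5 to 11 points. About 4 of those points come from Fisher's conservatism, as the working shows.

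Fourth, a reader might assume that UT grade is available as a second covariate for everyone. The weekly UT-grade endpoint in section 2 suggests routine grading, but patients who enter by the alternative route need no grade, so complete availability is not established.

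Fifth, timing. Enrolment ended in July 2022; 16 weeks later is about late November 2022, and the article is dated 1 December 2022. Section 2 describes the overarching study as open-label. Changing the published primary test when most week-16 outcomes have been collected has a credibility cost. This limits how the change can be made but does not remove the case for it.

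An unseen statistical analysis plan may add adjusted sensitivity analyses. That would not alter the primary test, which the article states.

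**Conclusion.** The point holds as a worthwhile, inexpensive gain in precision, not as a correction of bias. The stated primary test leaves out a baseline measurement that the trial collects and does not stratify on. If size is prognostic at a log odds ratio of -0.4 to -1.0 per SD, adjustment is worth about 1 to 7 points of power at 90 per arm, like for like. It would also remove most of a chance shift of about 1.6 to 4 points (0.2 to 0.6 standard errors) that a 0.2 SD imbalance would cause. If size is not prognostic, the covariate gains nothing and costs almost nothing.

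The direction is secure. The size rests on the assumed slopes, and the trial's own pooled data, without arm, could show which is nearest. The case for depth is weaker than the case for size, because grade may not exist for every patient.

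**What to change.** 1. Make the primary analysis a logistic regression of week-16 healing on arm, log baseline wound area, amputation status and ABI stratum. Name one inclusion-visit measure of area in advance (for example the product of the two diameters, or the traced area).
2. Report the standardised (marginal) difference in healed proportion with its 95% confidence interval, so that the result stays on the scale of the planned 20-point difference.
3. Add UT grade only if it is recorded at baseline for all patients, including those with amputation or dehiscent wounds, or with a pre-stated category for ungraded wounds.
4. Fix the model in a dated amendment before database lock and before any analyst sees outcomes by arm.
5. Keep Fisher's test as a reported sensitivity analysis.

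**Cost.** No new patients are needed, and no new data for the size adjustment. The primary result will depend on a fitted model, although in a randomised trial the standardised risk difference does not require that model to be correct. There will also be a late change to the published primary test, which must be documented openly.
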